### Secondary outcomes

#### Smart monitoring devices

Used in this study are the Electronic wristbands, which have a battery life of 30 days and are worn on the dominant hand to measure step count, heart rate, and blood oxygen saturation levels, providing an objective quantification of daily activity and cardiopulmonary function. Data from the wristband are collected via separate Gmail accounts for each participant and extracted into Excel documents using the mobile application. The parameters obtained are based on the 30-day averages of the aforementioned variables.

#### Exercise adherence

Is calculated as the percentage of personal activity participation times relative to the total number of interventions.

### Data collection and management

The data collection team consists of two medical graduate students and one community worker, primarily operating at rural community service centers. Data collectors must undergo standardized training and be fluent in local dialects. Table 2 shows the five measurement time points: baseline before randomization (T0), mid-intervention (T1), post-intervention (T2), and follow-up (T3 and T4). After data collection, participants’ identities will be anonymized using initial-number combinations, and handwritten records will be digitized. Two researchers will independently enter data into Excel. Software tools will detect inconsistencies and generate reports. After verification and cross-checking, data will be stored in an electronic database accessible only to principal investigators, data consultants, and data entry staff.

**Table 2 Tab2:**
[figure not shown]
Study assessment points and timelines

### Data analysis

SPSS 26.0 software was used for statistical analysis, with a significance level set at *p* < 0.05. Initially, the Shapiro-Wilk test will be employed to assess the normality assumption for quantitative data. Based on these results, appropriate statistical methods will be selected to compare participants’ demographic and other baseline characteristics before the intervention. If the data are normally distributed, an independent-sample t-test will be utilized; otherwise, the Mann-Whitney *U* test will be applied. The primary outcome measures, continuous variables, were analyzed using generalized estimating equations (GEEs). In cases of significant interactions between group and time factors, a simple effects analysis will be conducted to elucidate the sources of the differences. If the simple effects analysis of time factors yields significant results, post hoc tests will be performed using the Sequential Bonferroni Procedure to identify specific time points of substantial differences. Secondary outcomes included descriptive statistics on exercise adherence after intervention.

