## Methods

### Study design and ethical consideration

A multi-center, four-arm, parallel-group, assessor-blind randomized controlled trial and will take place in four rural communities of Huzhou City, northern Zhejiang, China. The study plan is designed to include three intervention groups: (a) static balance training combined with hand training; (b) dynamic balance training combined with hand training; (c) combined static and dynamic balance training with hand training; and control group (physical and health education).The study process is illustrated in Fig. 1. This study adheres to the CONSORT statement and SPIRIT guidelines [17, 18]. The primary or secondary outcomes were not expected to change during the course of the study. All results were specified in the protocol registered in the Chinese Clinical Trial Register (ChiCTR2500097310). It has been approved by the Medical Ethics Committee of Huzhou University (approval number: 202412-05).

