### Sample size

Based on a previous study evaluating the impact of proprioceptive balance training on posture control in older adults [19], G*Power 3.1 was used for power analysis to determine the required sample size for detecting a statistically significant effect of the intervention [20]. The significance level (α) was set at 0.05, and the statistical power was set at 0.80. To account for an anticipated 10% dropout rate over the 16-week study period, 33 participants will be recruited per group.

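### Baseline comparison of four arms is specified with two-group tests, and the role of T0 in the GEE should be stated

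*Protocol article*

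**What the plan says.** The Study design section describes "A multi-center, four-arm, parallel-group, assessor-blind randomized controlled trial". Under Randomization, allocation concealment, and blinding, representatives of four communities draw envelopes, so each arm is one community.

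The Data analysis section starts with a Shapiro-Wilk test on quantitative data, after which "appropriate statistical methods will be selected to compare participants’ demographic and other baseline characteristics before the intervention". It then names the methods: "If the data are normally distributed, an independent-sample t-test will be utilized", and the Mann-Whitney U test if not. No test for more than two groups appears. The only multiplicity procedure in the section, Sequential Bonferroni, is tied to post hoc comparisons of time points.

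The primary outcomes go into GEEs. The only model terms mentioned are group and time: "In cases of significant interactions between group and time factors, a simple effects analysis will be conducted". No covariate is named. The Data collection and management section counts T0 among the repeated measurements: "Table 2 shows the five measurement time points: baseline before randomization (T0" and four later assessments.

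**The concern.** A t-test or a Mann-Whitney test compares two samples and cannot give one comparison of four arms. An analyst following the text must choose which pairs to test and how to treat the resulting set of p-values, and the article guides neither choice. The likely results are an inflated number of apparent imbalances, or a choice of pairs made after the data are seen.

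The setting makes this more awkward. Each arm is a different community, so real baseline differences are plausible, and a p-value neither measures their importance nor corrects them. What matters more is how the baseline value of each outcome enters the primary model. The article leaves that to be inferred.

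**Working it through.** **Inputs from the article.** There are four arms (Study design section), 33 participants per arm and a significance level of 0.05 (Sample size section). The stated total reproduces: 4 × 33 = 132. The article gives no figure for the baseline tests, no effect size or SD, and no correlation between T0 and later values.

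**Step 1: number of comparisons.** Four arms give 4 × 3 / 2 = 6 pairs, of which 3 involve the control arm.

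**Step 2: chance of at least one false imbalance per quantitative variable.** This assumes no true difference and independent participants. If the tests were independent, the chance would be 1 − 0.95^6 = 26.5% for six tests and 1 − 0.95^3 = 14.3% for three. Pairwise tests share arms and are correlated, so the rates were simulated (normal data, 33 per arm, 100,000 runs):

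| Procedure at 0.05 | False imbalance per variable |
|---|---|
| One four-group ANOVA | 5.0% |
| Three t-tests against control | 12.6% |
| All six pairwise t-tests | 20.4% |

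**Step 3: clustering.** These rates treat participants as independent. With one community per arm and intraclass correlation ρ, a nominal 5% pairwise test at n = 33 has type I error 2[1 − Φ(1.96 × √(((1−ρ)/n) / (ρ + (1−ρ)/n)))]. For an assumed ρ of 0.01 this is 2[1 − Φ(1.96 × √(0.030/0.040))] = 9%. For ρ = 0.05 it is 2[1 − Φ(1.96 × √(0.0288/0.0788))] = 24%. A four-group test on participants has the same weakness, which favours description without p-values.

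**Step 4: role of T0 in the GEE.** Suppose T0 is a level of time, the group-by-time means are unrestricted and the data are complete. The interaction contrast at a later visit is then a difference between arms in mean change from T0. Per unit SD², with correlation r between T0 and that visit and equal variances, the contrast variance is proportional to:

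- change from T0: 2(1 − r)
- T0 as covariate: 1 − r²
- ratio: (1 − r²) / [2(1 − r)] = (1 + r)/2

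| Assumed r | Change | Covariate | Ratio |
|---|---|---|---|
| 0.3 | 1.40 | 0.91 | 0.65 |
| 0.5 | 1.00 | 0.75 | 0.75 |
| 0.7 | 0.60 | 0.51 | 0.85 |
| 0.9 | 0.20 | 0.19 | 0.95 |

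The ratio holds only if the arms have equal expected baselines and participants are independent.

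**The case against.** The baseline tests do not feed the primary analysis, so the error stays in the descriptive table. That is right, and it limits the weight of the point.

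A reader might infer that the comparability tests are invalid. They are not: each t-test is a proper test of its own pair if observations are independent. What is missing is a test that fits four groups and a rule for handling several pairs. The text does not say that all six pairs will be tested, and three comparisons with control fit it equally well, so both rates are shown.

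A reader might also multiply all nine items under Basic information by six pairs, giving 54 tests and 54 × 0.05 = 2.7 expected false positives. The section ties the choice of test to quantitative data. Gender, education, marital status and living alone are ordinarily categorical, which leaves about five items: 5 × 6 = 30 tests and 30 × 0.05 = 1.5, and that only if communities do not truly differ.

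The stronger reading of the GEE text is that T0 is excluded as a covariate and precision is lost. The article does not say so. It is silent, and covariate lists are commonly left to a fuller plan. T0 as a time level is the natural reading, and such a model already uses the baseline. Nor can a power gain be quoted. A rise from 68% to 80% at r = 0.5, for example, follows only from setting adjusted power at 80% and working backwards: Φ(2.80 × √0.75 − 1.96) = 0.68.

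Finally, covariate adjustment is not plainly better here. If communities differ at baseline, change-score and adjusted analyses answer different questions and may disagree. This objection stands and shapes the recommendation.

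**Conclusion.** The mismatch is certain on the face of the article: two-group tests are prescribed for a four-arm comparison. If they are applied to all six pairs at 0.05, the false-imbalance rate per quantitative variable is about 20% (about 13% for three comparisons with control), against 5% for one four-group test. These rates assume independent participants and no true differences. The consequence is confined to the baseline table.

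The T0 point is secondary and rests on inference. If T0 is a level of time, using it as a covariate would cut contrast variance by 35% at r = 0.3 and by 5% at r = 0.9. Here r is assumed, and equal expected baselines are required, which one community per arm puts in doubt. Neither change removes the complete confounding of arm with community.

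**What to change.** 1. Delete the t-test and Mann-Whitney sentence and report baseline characteristics by arm without p-values. If a test is kept, name one four-group test per variable: ANOVA or Kruskal-Wallis for quantitative items, chi-square or Fisher for categorical ones.
2. State how T0 enters the GEE. Preferably take T1 to T4 as responses with the T0 value of the same outcome as a covariate.
3. Report the change-from-T0 analysis as a sensitivity analysis, and say that neither analysis separates arm from community.

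The cost is analysis wording plus one additional model run per outcome. T0 is already scheduled for collection, so no new data are needed. The downside is that the two analyses may disagree if communities differ at baseline, and that would have to be reported openly.

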**Methods:**

A single-blind, four-group parallel, multicenter randomized controlled trial was used. Four rural communities in Huzhou, Zhejiang Province, were included in the study, with an estimated total sample size of 132 individuals. During the 16-week intervention period, the comprehensive exercise program consisted of two balance training programs and one hand training session provided by a multidisciplinary team including physiotherapists, sports professionals, nurses and community health workers. The four rural communities were randomly divided into four experimental groups in the ratio of 1:1:1:1 (a) static balance training combined with hand training; (b) dynamic balance training combined with a hand training program; (c) multi-modal static-dynamic balance and hand function training (M-mBHF) program; and (d) a Daily activity group. The multidimensional balance ability, hand function, and life-space mobility of the four parallel groups will be assessed at baseline (T0), 8 weeks of intervention (T1), 16 weeks of intervention (T2), and at 24 (T3) and 32 weeks (T4) follow-up.

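### GEE with no weighting stated is fixed for the continuous primary outcomes over five visits; a likelihood mixed model needs a weaker dropout assumption at little cost

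*Protocol article*

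**What the plan says.** The Data analysis section of the protocol article names the method: "The primary outcome measures, continuous variables, were analyzed using generalized estimating equations (GEEs". The model contains group, time and their interaction, and the interaction opens the next step: "In cases of significant interactions between group and time factors, a simple effects analysis will be conducted". The software is SPSS 26.0. The section names no weighting, imputation or working correlation.

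The data will be longitudinal and incomplete. Under Data collection and management, "Table 2 shows the five measurement time points". The Abstract (Methods) places the later ones at "16 weeks of intervention (T2), and at 24 (T3) and 32 weeks (T4) follow-up". The Sample size section says: "To account for an anticipated 10% dropout rate over the 16-week study period, 33 participants will be recruited per group". No dropout figure is given for weeks 16 to 32.

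**The concern.** Ordinary GEE without weights is in general consistent only when dropout is completely random. A likelihood-based mixed model on the same records is valid under the weaker condition that dropout depends on values already observed, provided that its mean and covariance are correctly specified.

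The design gives some reason to doubt completely random dropout. The Intervention group section describes two sessions a week, one of them at home without in-person supervision, with increasing difficulty. The Control group section describes one 40-minute education session a week. A participant with poor balance may have more reason to leave training than to leave education. If so, those remaining in training look better than the arm as a whole, and part of an apparent group-by-time interaction could be selection. Loss accumulates, so any such bias would weigh most on T3 and T4, which carry the long-term claims.

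This point is about the method that the article commits to. It does not complain that a missing-data policy is absent.

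**Working it through.** **Inputs from the article.** Five visits; 33 per arm; 132 in total; 10% dropout by week 16; GEE with group, time and interaction.

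**Inputs assumed.** Within-person correlation; strength and direction of value-dependent dropout; dropout after week 16. The article gives none of these.

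**Step 1: the plan's own figure.** 4 × 33 = 132, as in the Abstract. 29/(1 − 0.10) = 32.2, rounded up to 33, so 33 fits 29 evaluable per arm. The power calculation cannot be rerun because the article gives no effect size or SD. The present point does not depend on it.

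**Step 2: where the bias comes from.** With a separate mean for each arm and visit and independence working correlation, the GEE estimate is the plain mean of those still present. For one arm,

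bias = p × (mean of stayers − mean of leavers), with p the share lost.

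The bias in the arm difference is one arm's term minus the other's, so it cancels when the mechanism is the same in both. A mixed model, or GEE with a realistic working correlation, uses each leaver's earlier values and so corrects much or all of it.

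**Step 3: no true effect.** Large-sample simulation with exchangeable correlation 0.6. Dropout in the training arm depends on the last observed value (log-odds 0.7 or 1.0 per SD), and dropout in the control arm is random. With a per-visit hazard of 0.05, controls lose 1 − 0.95² = 9.75% by T2 and 1 − 0.95⁴ = 18.5% by T4. The training arm loses about 12-14% and 22-25%.

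- Independence GEE: bias about 0.05-0.08 SD at T2 and 0.09-0.15 SD at T4.
- Exchangeable GEE: at most 0.025 SD.
- Likelihood model: at most about 0.01 SD.
- Same mechanism in both arms, independence GEE: at most 0.006 SD.

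Check with the Step 2 formula: 0.05/0.12 = 0.42, 0.08/0.14 = 0.57, 0.09/0.22 = 0.41 and 0.15/0.25 = 0.60. Leavers would have to be about 0.4-0.6 SD worse than stayers at that visit.

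**Step 4: true difference 0.50 SD, steeper dropout.** 200,000 per arm, slope 1.5 per SD, exchangeable 0.6 or AR(1) 0.85 correlation. The ranges are estimated differences.

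| Scenario | Independence GEE | Mixed model, unstructured |
|---|---|---|
| 10% lost, value-dependent in one arm (T2, T4) | 0.57-0.60 | 0.50 |
| 10% lost, opposite directions in the two arms (T2, T4) | 0.65-0.70 | 0.50 |
| 20% lost by T4 (assumed), one arm (T4) | 0.66 | 0.49-0.51 |
| 20% lost by T4 (assumed), opposite directions (T4) | 0.80-0.84 | 0.50 |
| Completely random, or same mechanism in both arms | about 0.50 | about 0.50 |

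Over the same scenarios exchangeable GEE gave 0.46-0.52 and unstructured GEE 0.50-0.54, a bias of about 0.04 SD or less.

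**Step 5: bias against precision at 33 per arm.** The SD of the estimate was 0.26-0.29 for independence GEE and 0.25-0.28 for the mixed model, so the change costs no precision. For a two-sided 5% test with δ = bias/SE, the rejection rate under no effect is Φ(−1.96 + δ) + Φ(−1.96 − δ).

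- T2, SE 0.27: δ = 0.05/0.27 = 0.19 to 0.08/0.27 = 0.30, giving about 5.4% to 6.0%.
- T4, SE 0.28: δ = 0.09/0.28 = 0.32 to 0.15/0.28 = 0.54, giving about 6% to 8%.

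**The case against.** The strongest reply is that the sizeable bias belongs to the independence working correlation and not to GEE as such. When the covariance is known, the likelihood estimate and GEE with that same working correlation solve the same equation, and exchangeable GEE was nearly unbiased in the runs. The article does not say that independence will be used. The absence of weights is also read from silence, and a full protocol or analysis plan could supply weights, imputation or a working correlation. This stands, and it limits the size of the problem.

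The arm difference in dropout is assumed. The three training arms share the same twice-weekly format, so the argument is weak for comparisons among them. Weekly telephone calls and WeChat contact with non-attenders may also reduce selective loss. This stands too.

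The remedy has limits. The Push and Release rating is ordinal, so a Gaussian model is only approximate for it, and neither method handles dropout that depends on unobserved values.

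What does not stand is that the choice is a matter of taste. The article commits to a method that in general needs the stronger assumption and leaves its most vulnerable form open. The alternative is available in the same software.

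**Conclusion.** The point holds as a recommended, inexpensive improvement. The method named needs completely random dropout in general, and a mixed model for the continuous outcomes needs less. The size is conditional: roughly 0.05-0.08 SD at T2 and 0.09-0.15 SD at T4 under independence working correlation with arm-specific, value-dependent dropout; about 0.04 SD or less under exchangeable or unstructured correlation; about zero if dropout works alike in all arms.

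Stronger readings are tempting but not supported. A reader might infer that the planned GEE will produce a false group-by-time interaction. The article fixes neither the working correlation nor a dropout pattern that would make this so, and at 33 per arm the T2 bias is only about 0.2-0.3 standard errors. A reader might also quote 0.16-0.20 SD at T4 from scenarios with 29-35% lost, or the larger Step 4 figures. Those losses and the steep or opposing dropout slopes have no source in the article. Nor does it anticipate at least 10% loss: it says 10%, and only to week 16.

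**What to change.** In the Data analysis section, make a REML linear mixed model for repeated measures the primary analysis of the continuous primary outcomes, with arm, visit, arm-by-visit, baseline value and unstructured within-person covariance, fitted with the MIXED procedure in SPSS. Keep GEE as a sensitivity analysis and name a working correlation other than independence. Analyse the 0-4 Push and Release rating separately, by a method suited to an ordinal outcome.

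The cost is a few sentences of protocol text and slightly more analysis work, with no change to visits, data collection or sample size. The downside is reliance on a modelled covariance, which the unstructured form and the GEE sensitivity analysis largely address. The change does not protect against dropout that depends on unobserved values. It also leaves the allocation of one community to each arm (Randomization, allocation concealment, and blinding) as it is: arm and community remain confounded under either method.

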## Discussion

To our knowledge, this study is designed as the first randomized controlled trial to investigate the potential effects of the multidisciplinary team-based M-mBHT program on rural older adults through four parallel groups with equal training doses over 16 weeks. Therefore, the design of this study protocol is expected to complement the existing gaps in balance and hand function training, potentially providing rural older adults with a low-cost and efficient exercise program.

Previous studies have shown that balance training is divided into static balance (i.e., static-continuous balance) and dynamic balance (i.e., dynamic-continuous, active, and reactive balance) exercises, comprising two-thirds of the total training time [31, 32]. Hand training, based on acupoint principles and constituting one-third of the time, uses massage and kneading to stimulate hand receptors, exciting the cerebral cortex [33], and boosting blood flow, flexibility, and strength. This provides a theoretical reference for the combination in the design of this research protocol, which is anticipated to contribute to improving the effectiveness of the integrated program for balance ability and hand function in rural older adults.

Interestingly, this study employs an innovative, comprehensive index system (multidimensional balance ability, hand function, life-space mobility, and intelligent monitoring device data) to evaluate the anticipated short-term and long-term effects of the M-mBHT program. Most outcome variables use objective assessment methods, which are expected to reduce measurement errors and risks associated with subjective evaluations. Additionally, we have constructed a complete assessment framework for balance ability (static, dynamic, proactive, reactive, and daily living balance), covering five dimensions. This framework is designed to comprehensively understand individual performance in balance and potentially identify focuses for subsequent improvements. A meta-analysis indicates that wearable technology interventions lasting more than 12 weeks can achieve more significant improvements in activity ability [34]. Electronic wristbands, as user-friendly and comfortable trackers, are intended to effectively monitor older adults’ daily activities and cardiopulmonary functions. The 16-week structured intervention across four multicenter groups, with outcomes evaluated at 2, 4, 6, and 8 months post-randomization, is designed to ensure ensures data continuity. This provides a time window to explore the effectiveness of the intervention programs at different stages and to investigate the impact of cycle factors on outcome indicators.

The M-mBHT program is comprehensive, incorporating sensory, progressive circulation, group supervision, and online integration. The decline in physical function and balance ability in older adults is often related to sensory weakness. Maintaining balance and engaging in exercise is theorized to require the coordinated action of sensory information such as vision, auditory, muscle tension, support surface, and vestibular sense in both static and dynamic states [26]. Considering the rural living environment, this study includes flat ground and safe, convenient sandy ground in balance training to change the contact surface. Visual and auditory deprivation and certain disturbances are also introduced. Repeated and intermittent visual occlusion **is** hypothesized to enhance balance training by potentially increasing cortical phase synchronization and improving information transmission efficiency and reaction speed [35]. Intermittent auditory deprivation aims to simulates real-life challenges, potentially increasing reliance on vision and proprioception, and thus may enhance muscle strength and balance outcomes. This approach is designed to be simple, with low venue requirements and minimal skill demands on seniors, aiming to ensure wide adaptability.

Considering the learning capabilities of older adult individuals, we established four WeChat groups to manage four groups. Teaching videos were created and uploaded to the WeChat public account for dissemination within the group chat, along with online support for addressing any issues encountered by participants. A review analyzing exercise compliance among older adults indicates that supervised training schemes generally exhibit higher adherence rates [36]. Participants who failed to attend on time were contacted via WeChat to enhance their motivation and ensure the timely completion of the program. Recognizing the impact of social isolation on function [37], the intervention aims to integrates person-environment fit, using local rural community centers to form neighborhood exercise groups, which may enhance social interaction. Delivering potentially effective exercises for rural seniors is complex and is expected to demands teamwork among diverse healthcare specialists. Experts in medicine, psychology, and sociology develop and review our programs. To enhance community medical services, the Chinese government has established medical alliances in recent years [38]. Given this context and the study hypothesis, combining institutional and community healthcare workers represents a proposed model for program implementation, anticipated to be effective based on available frameworks.

The proposed M-mBHT program has several limitations that may influence the generalizability of findings. First, due to the limited number of research sites, the sample may not be fully representative of China’s rural older adults. Second, the absence of muscle mass assessment could be a limiting factor, as the 16-week intervention period might not be sufficient to observe significant increases in muscle mass among older adult participants. Additionally, because of the nature of the intervention, participants were not blinded, which may be a potential limitation in maintaining objectivity in the assessment of self-reported outcomes. Finally, effectively integrating rural community resources under national rural policy guidelines to provide scientifically sound and feasible exercise programs for older adults remains a unique challenge. Future multi-center, large-scale randomized controlled trials (RCTs) are necessary to further validate the research findings regarding the impact of the M-mBHT program on the health management of rural older adults.

In the context of healthy aging and changing socio-demographic changes, maintaining the multidimensional balance ability (static, dynamic, proactive, reactive, and daily living balance), hand function (grip strength and manual dexterity), and life-space mobility of vulnerable groups such as rural older adults is essential for promoting health equity and achieving healthy aging. Thus, a high-quality research protocol design is expected to be crucial for establishing scientific principles and potentially improving the activity levels and balance ability and functional status of rural residents. If the hypothesized benefits are observed, the findings may contribute to evidence-based strategies for enhancing functional health in rural older adults. However, definitive conclusions await the trial’s completion and data analysis.

